#### Secondary outcome measures

The preoperative results of the thermal pulp test and the electric pulp test will be recorded to ensure pulp necrosis of the involved tooth. The test results during the follow-up will be used to determine if the teeth included in the study regain sensitivity.
The results of thermal pulp test are as follows:
*Normal*. The test tooth is considered normal if the patient responds similarly to when a control tooth is tested.*Sensitive*. The test tooth is considered sensitive if the patient experiences more pain than when a control tooth is tested.*Dull*. The test tooth is considered dull if the patient has a much slower, reduced response when stimulated compared to when a control tooth is tested at the same temperature.*No response*. The tested tooth is considered to have no response if the patient does not respond to stimulation.The results of electric pulp test are as follows:
The numerical reading is recorded when the patient elicits a response. To ensure consistency, each tooth will be tested twice and the average result will be used in the analyses.

#### Safety evaluation

All information regarding adverse events during the study will be recorded in detail, including symptoms, signs, onset time, and severity. Some possible adverse events that may be attributed to RET include reinfection of the root canal, external root resorption, internal root resorption, and discolouration.

### Sample size and statistical methods

#### Sample size

The primary outcome measure is the success rate at 24 months after treatment. According to nQuery Advenced 8.6 software (Statistical Solutions Ltd., Cork, Ireland), a sample size of 346 (173 for each group) patients is required when α = 0.05 and the test power is 80%.

#### Data collection methods and data management

Data associated with this study will be collected in the standardised case report form (CRF) for the outcome analysis, and a specific supervisor will be responsible for reviewing the integrity, accuracy, and consistency of the data. To ensure the accuracy of data entry, two researchers will be responsible for entering the data independently and data query forms (DQF) will be resolved by tracing the source data. All the data will be registered in document clouds, and only authorised researchers will have access. Data monitoring committee consists of the Department of Biomedical Statistics, Southern Medical University, independent from the sponsor and competing interests.

As for the audition of this study, the frequency is once a year. During the audition, the project organisation will review the test process and make a comprehensive evaluation. The process will be independent of investigators and the sponsor.

#### Statistical analysis

The data will be analysed by an independent statistician using SPSS 20.0 software (IBM Co., Armonk, NY, USA) at the end of the study to evaluate the evolution. The continuous variables will be described as the mean (standard deviation) or median and analysed using parametric methods. Categorical variables will be described as percentages and analysed using non-parametric methods. The level of significance will be *P* < 0.05, and 95% confidence intervals will be calculated.
*Baseline analysis*

The two groups will be comparable in terms of sex, age, tooth position, disease type, and apical hole size. Quantitative variables will be analysed using a one-way analysis of variance (independent sample t-test) or non-parametric methods if the data do not meet and cannot be transformed to meet parametric assumptions. Qualitative variables will be analysed using the Wilcoxon rank-sum test. A principal component analysis will be performed using multinomial logistic regression to adjust for potential confounders.
(2)*Main outcome analysis*

The inter-group comparison of success rates will be analysed using the chi-square test. If there are baseline variables influencing the comparability of the two groups, a logistic regression model will be used to eliminate the effects of these confounders on the success rate and the odds ratio (OR) will be calculated. For the missing data, the last observation carry forward method will be adopted to fill the validity analysis, that is, the case data that fails to observe the whole treatment process will be transferred to the final result of the test with the last observation data.
(3)*Secondary outcome analysis*

For intra-group comparisons, McNemar’s test will be used to analyse the clinical outcomes of different centres. For inter-group comparisons, the secondary outcome will be analysed using the Chi-square test.
(4)*Safety evaluation analysis*

The adverse events that occur during the study period will be listed for each group and compared using the chi-square test. The security evaluation does not evaluate missing data.

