**Fig. 2 Fig2:**
[figure not shown]
Schedule of intervention and assessments. All study-related procedures are outlined in this figure. RET, regenerative endodontic therapy; CBCT, cone beam computed tomography

The primary objective of this study is to evaluate the efficacy of RET and RET with i-PRF for the treatment of mature permanent teeth with pulp necrosis. The secondary aim is to carefully investigate the factors influencing the clinical outcomes of RET in mature permanent teeth with pulp necrosis, and at the same time, to explore the standard RET protocol for treating mature permanent teeth with pulp necrosis.

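### The only unconditional multivariable step, a principal component analysis done by multinomial logistic regression, cannot be carried out as described, and the text shown gives the secondary aim no workable prespecified analysis

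*Protocol article*

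**What the plan says.** Study design and objectives sets the aim: "The secondary aim is to carefully investigate the factors influencing the clinical outcomes of RET in mature permanent teeth with pulp necrosis".

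Statistical analysis contains two multivariable steps.

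- **Baseline analysis.** After naming the variables on which the arms are to be compared ("The two groups will be comparable in terms of sex, age, tooth position, disease type, and apical hole size"), the article states without condition: "A principal component analysis will be performed using multinomial logistic regression to adjust for potential confounders". It names no outcome for this step.
- **Main outcome analysis.** The primary comparison is unadjusted: "The inter-group comparison of success rates will be analysed using the chi-square test". A regression follows only on a condition: "If there are baseline variables influencing the comparability of the two groups, a logistic regression model will be used". Its purpose is to "eliminate the effects of these confounders on the success rate and the odds ratio (OR) will be calculated".

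The other analyses listed are univariate baseline comparisons, McNemar's test within groups, and chi-square tests between groups for the secondary outcome and for adverse events. None of the analyses is named as the one that serves the secondary aim.

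**The concern.** The Baseline analysis sentence joins two techniques that do different jobs and gives the combination a third job that neither does in that form. An analyst could not follow it without inventing something: which outcome, which variables go into the components, how many components to keep, and what is then regressed on what.

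This is not detail held back for a fuller document. It is a positive statement of a method, and the method is misdescribed. An analysis plan that follows it inherits the error, and one that departs from it contradicts the published protocol.

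The secondary aim is also at stake. If neither multivariable step can estimate how a baseline factor relates to success, the choice of factors and model is made after the data are seen, which is what prespecification should prevent.

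**Working it through.** The point concerns method, so no figure in the plan tests it directly. The stated 346 patients cannot be reproduced, because the Sample size section gives no success rates, but nothing below depends on how that number was reached.

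**1. Can the PCA step be carried out as written?**

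- PCA is computed from the covariance or correlation matrix of the covariates alone. No outcome enters, so the loadings are the same whatever the success data show. It is not performed by any regression.
- A component or loading does not adjust a treatment comparison. Adjustment happens only when something is entered as a covariate in an outcome model, and the sentence names no such model.
- Primary outcome measures defines two classes, success and failure. With two classes, multinomial logistic regression reduces to binary logistic regression, so the word adds nothing for this outcome.
- Suppose the sentence means PCA first, then regression on the component scores. Three of the five listed variables (sex, tooth position, disease type) are categorical, which ordinary PCA handles poorly. A component that mixes them with age and apical size has no coefficient for any single factor.

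**2. Does the conditional logistic model serve the aim?**

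It selects variables by imbalance between the arms, not by their relation to outcome, and treats them as nuisances to be removed. The trigger is not defined. Assume it is a baseline test on any of the 5 listed variables, with independent tests and sound randomisation:

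- trigger P < 0.05: the model runs with probability 1 − 0.95^5 = 0.226; a given factor qualifies with probability 0.05;
- trigger P < 0.10: 1 − 0.90^5 = 0.410; a given factor qualifies with probability 0.10.

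These chances are the same however strongly the factor predicts success.

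**3. Could a factor model be fitted from the planned data?**

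The article gives no failure rate, so a range is assumed, with an outcome available for all 346 patients. The coefficients for the model proposed under the fix are: arm 1, centre 2 (three centres), sex 1, age 1, tooth position 2, disease type 2, apical size 1, a total of 10. The counts for tooth position and disease type are assumptions, as the article does not give their categories. A separate lesion term would make 11.

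| Assumed failure rate | Failures (346 × rate) | Per coefficient, 10 | Per coefficient, 11 |
|---|---|---|---|
| 10% | 34.6 | 3.5 | 3.1 |
| 15% | 51.9 | 5.2 | 4.7 |
| 20% | 69.2 | 6.9 | 6.3 |
| 30% | 103.8 | 10.4 | 9.4 |

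A factor model is possible, but at low failure rates it should be small or penalised. The table bears on the design of the replacement. It is not evidence of the error.

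**The case against.** The strongest reply is that the sentence sits under Baseline analysis and is given the purpose of confounder adjustment. Nothing ties it to the secondary aim, so even a correctly worded version would not be the stated factor analysis. That is right. A reader might infer that this one sentence leaves the secondary aim without a usable answer, and the document does not support that. The supportable statement rests on both multivariable steps together: one is misdescribed, and the other is conditional and differently aimed.

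A second reply is that a missing factor model may simply have been left to an analysis plan or full protocol. As a bare absence it would be no finding. What is criticised is a method stated wrongly; the lack of a workable analysis is its consequence within the text shown.

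Third, the sentence names no outcome, and the thermal pulp test under Secondary outcome measures has four classes, for which a multinomial model is possible. This also stands in part: the word multinomial is not in itself an error. But Secondary outcome analysis assigns the between-group comparison of that outcome to a chi-square test, and no choice of outcome turns PCA into something done by regression.

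Fourth, component scores used as covariates would be a genuine adjustment. That is so, but the sentence does not describe it, and it would still say nothing about single factors.

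Finally, a reader might conclude that a well-balanced prognostic factor would never be estimated. That is too strong. Main outcome analysis does name a valid logistic regression with an odds ratio, its trigger is not defined as a P-value rule, and the factors and the outcome are recorded.

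**Conclusion.** Wrong as written. The unconditional multivariable step cannot be carried out as described, and no reasonable reading of it would identify which factor influences outcome. The conditional model picks factors by chance imbalance: under the assumed rules it would run about 23% to 41% of the time, and a given factor would qualify about 5% to 10% of the time. The text shown therefore gives the secondary aim no workable prespecified analysis.

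The reach is limited. The aim stays answerable from data the trial already collects. The primary chi-square comparison and the safety analysis are untouched. The reasoning about PCA rests on no assumption; the trigger probabilities and failures per coefficient rest on the assumptions stated with them and only indicate scale. The correction should be made before analysis, and nothing in the trial's conduct depends on it.

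**What to change.** Delete the PCA sentence. In its place, prespecify one binary logistic regression of 24-month success on treatment arm, centre, sex, age, tooth position, disease type and apical size, all entered together whatever their baseline balance and with no selection by P value. Add baseline periapical lesion only if disease type, which the article does not define, does not already encode it. Report each odds ratio with its 95% confidence interval, state that the model serves the secondary aim, and label it exploratory.

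If failures prove few, limit the number of coefficients or use a penalised fit such as Firth's. This is optional and one reasonable choice among several.

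The cost is wording in the protocol and analysis plan. The five baseline variables are already listed, and CBCT is already scheduled at baseline should lesion status be needed. The plan already intends a logistic regression in SPSS 20.0; only a penalised fit might need R or an SPSS extension.

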## Methods

### Study design and objectives

This is a randomised, double-blind, parallel positive control, multicentre clinical trial (Fig. 1) that aims to compare the efficacy of i-PRF and blood clots (BCs) as scaffolds in RET for mature permanent teeth with pulp necrosis. The protocol will be reported according to the Standard Protocol Items: Recommendations for Interventional Trials (SPIRIT) statement (Additional file 1). After informed consent acquisition, all eligible patients (*n* = 346) will be randomly divided into two groups at an allocation ratio of 1:1. Patients in the test group will receive RET with i-PRF while those in the control group will receive conventional RET with BC. The follow-up period will be 24 months, and clinical data will be collected at 1, 3, 6, 12, 18, and 24 months after surgery. Figure 2 outlines the schedule of events for patients in the trial.

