### Randomisation, allocation, and blinding

Eligible patients will be randomly assigned to one of two groups at an allocation ratio of 1:1. The randomisation sequence and grouping will be generated and stored by one researcher who will not be involved directly in participant screening, enrolment, or assessment, using SPSS 20.0 software (IBM Co., Armonk, NY, USA). All random numbers will be listed sequentially, and a set of 10 numbers will be arranged as a cluster (the first 5 for the test group and the last 5 for the control group). Then, random numbers and grouping are inserted in opaque and sealed envelopes sequentially. After all the envelopes have been sealed, they will be distributed to each research centre. Only dentists can open the envelope to check the group allocation and perform the interventions according to the instructions of this study. As a double-blind trial, the patients and outcome evaluators will be blinded to the group assignment until the completion of the study. As dentists cannot be blinded to treatment allocation due to the notable differences in the treatment methods, they will not be allowed to discuss the type of intervention with either patients or outcome evaluators.

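### Adjustment of the primary result hinges on observed baseline imbalance, with no trigger, covariate list or rule of precedence; two baseline methods are mis-stated; one stratified analysis fixed in advance would be better

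*Protocol article*

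**What the plan says.** All of this stands in the protocol article under Statistical analysis, unless noted.

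- **Main outcome analysis.** Success rates are compared by chi-square test, without any condition. The next sentence adds a model: "If there are baseline variables influencing the comparability of the two groups, a logistic regression model will be used to eliminate the effects". An odds ratio is then calculated.
- **Baseline analysis.** Five variables are listed for comparison between the groups: sex, age, position of the tooth, type of disease and size of the apical opening. Quantitative variables get a t-test/ANOVA or a non-parametric method. For the others: "Qualitative variables will be analysed using the Wilcoxon rank-sum test". Then: "A principal component analysis will be performed using multinomial logistic regression to adjust for potential confounders". The general significance level is P < 0.05.
- **Centre.** It is in neither the baseline list nor the primary analysis. Its one mention in the analysis is a McNemar test within groups, under Secondary outcome analysis. Study setting and recruitment names three centres. Randomisation, allocation, and blinding says that envelopes are sent to each of them.
- **Lesion.** Inclusion criteria admit teeth with or without a periapical lesion. Primary outcome measures counts either no apical shadow or a smaller one as radiographic success.

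**The concern.** Under 1:1 randomisation any baseline difference between the groups is chance. Whether a covariate deserves adjustment depends on how well it predicts the outcome, not on whether it happens to be unbalanced. A rule driven by imbalance therefore adjusts for the wrong reason, and it leaves three things open until the data are seen: what sets it off, which covariates go in, and whether the chi-square or the adjusted odds ratio is the trial's answer when they disagree.

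Two of the named methods are also wrong as written. A rank test needs an order. For tooth position its P value depends on how the categories happen to be numbered. Principal component analysis and multinomial logistic regression are different techniques, and one is not carried out by means of the other.

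Lastly, two factors known at baseline are not fixed in the stated primary analysis. One is centre. The other is lesion status, which shapes the endpoint itself: a tooth with a lesion succeeds radiographically if the shadow shrinks or disappears, while a tooth without one has only to avoid a new shadow.

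**Working it through.** **1. The plan's own figure.** The article gives "a sample size of 346 (173 for each group) patients" at α = 0.05 and 80% power but no success rates, difference or dropout. The figure can be neither reproduced nor refuted. Several two-sided assumptions reach 173 per group, for example 40% v 55% without dropout, or 65% v 80% with 20% dropout. At 173 per group the detectable difference is about 75% v 87%. The points below use n = 173 per group and do not alter it.

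**2. How often a significance trigger would fire.** Inputs: five variables (Baseline analysis) and P < 0.05 (Statistical analysis). Assumed: each variable is tested at that level, the tests are independent, and one significant result is enough.

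1 − 0.95^5 = 1 − 0.774 = 0.226, about 23%.

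**3. What such a switch does.** 3,000 simulated trials of 346 per setting; assumed success about 75% v 87%; five covariates with no, moderate or strong prognostic effect. The two-stage rule adjusts only for variables flagged at 5%.

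| Covariates | Type I error: chi-square / two-stage | Power: chi-square / two-stage / fixed covariates plus centre |
|---|---|---|
| Not prognostic | 4.7% / 4.8% | 82.0% / 81.8% / 81.8% |
| Moderate | 5.2% / 5.0% | 82.0% / 81.8% / 83.9% |
| Strong | 4.8% / 4.5% | 89.0% / 88.8% / 92.5% |

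The switch gains no power over the crude test. It changes the significance verdict in about 0.3 to 1.3% of trials.

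**4. Fixed adjustment for lesion.** Assumed: odds ratio 2.5 and the control success rates shown. 20,000 simulated trials per row, crude chi-square v Mantel-Haenszel stratified on lesion.

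| Control success, no lesion / lesion | Share with lesion | Crude | Stratified | Gain (points) |
|---|---|---|---|---|
| 97% / 50% | 50% | 76.8% | 85.6% | 8.8 |
| 95% / 60% | 50% | 78.5% | 83.6% | 5.1 |
| 90% / 70% | 50% | 80.1% | 81.6% | 1.5 |
| 85% / 75% | 50% | 82.7% | 82.7% | 0 |
| 90% / 80% | 50% | 71.9% | 71.6% | −0.3 (none) |

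With lesions in 80% of teeth, the gains in the first two rows fall to about 2.1 and 1.2 points. Type I error was about 5% for both tests.

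Hand check of the first row:
- An odds ratio of 2.5 turns 0.97 into 0.988 and 0.50 into 0.714. The group means are 0.735 and 0.851, a difference of 0.116.
- Crude variance: 0.735 × 0.265 + 0.851 × 0.149 = 0.322. SE = √(0.322/173) = 0.0431. z = 2.69. Power = Φ(2.69 − 1.96) = 77%.
- Mean within-stratum variance: (0.97 × 0.03 + 0.50 × 0.50)/2 + (0.988 × 0.012 + 0.714 × 0.286)/2 = 0.248. SE = √(0.248/173) = 0.0378. z = 3.07. Power = Φ(3.07 − 1.96) = 87%.

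Both agree with the simulation to about a point.

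**5. Fixed adjustment for centre alone.** 6,000 trials per setting, three centres differing by ±0.3 or ±0.7 on the log-odds scale. Gains run from 0.1 points (84.1% v 84.2%) to 1.3 points (82.7% v 84.0%).

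**6. The Wilcoxon test.** For a two-level variable such as sex, it is essentially the chi-square test and does no harm. It fails for unordered variables with three or more levels: tooth position, and probably type of disease.

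**The case against.** The strongest reply is that a default test is named without condition. The logistic model may be meant as supportive, since nothing says that its odds ratio replaces the chi-square. That stands. A reader might infer that the primary result is undefined. The text does not go so far: only the trigger, the covariates and the order of precedence are open.

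A reader might also infer that baseline significance tests decide the analysis. The article states no such trigger. The baseline section just before makes it likely, but judgement about comparability is another reading, and the 23% does not apply under that reading. Judgement would be no better pre-specified.

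Third, the power gain rests on assumptions, because lesion prevalence, lesion effect and success rates are all missing from the article. This stands too, and with gaps of 10 points between lesion and no-lesion teeth there is no gain.

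Fourth, a journal article may leave centre terms and covariate lists to an analysis plan that is not shown, and type of disease may be meant to cover lesion status. So silence on centre is not in itself an error. The imbalance rule, the rank test and the principal-component sentence are different: the article states them, and a later plan that merely elaborated them would keep the fault. Even if type of disease means lesion, it would be adjusted for only when unbalanced.

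**Conclusion.** The point holds in a limited form. Adjustment of the primary result is tied to observed imbalance, with no trigger, covariate list or rule of precedence, and two baseline methods are mis-stated.

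It would be tempting to say that the switch invalidates the test or costs the trial a large share of its power. Neither is supported. Type I error of the two-stage rule was 4.5 to 5.0% in simulation, and its power matches that of the chi-square. What is lost is pre-specification, plus whatever fixed adjustment would have gained: about 0 to 9 points for lesion, depending wholly on assumed prevalence and prognostic strength, and about 1 point for centre. The 23% depends on an inferred P < 0.05 trigger and five independent variables.

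The change is worth making, but the trial does not fail without it.

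**What to change.** Pre-specify one primary analysis: a Mantel-Haenszel comparison of 24-month success, stratified by centre and by baseline periapical lesion (yes/no), reported as a stratified risk difference with 95% CI. Three centres by two lesion classes make six strata, on average 346/6 ≈ 58 patients each. Name this as the result that decides the trial, and keep the crude chi-square as a sensitivity analysis.

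Remove the model triggered by imbalance. Describe the baseline variables by group without tests, and delete the Wilcoxon and principal-component sentences. If type of disease is meant to record lesion status, say so.

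The cost is wording. Centre is known for every patient, and the baseline CBCT described under Outcome measures already records the apical shadow. No patients, visits or measurements are added, and 346 stands. The article describes the trial as still recruiting, with analysis at the end of the study. The change should be dated and made before outcome data are seen by group.

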### Outcome measures

Variables will be measured at baseline and at 1, 3, 6, 12, 18, and 24 months after the treatment. At each appointment, a clinical examination, a periapical radiograph, and pulp tests (thermal and electric) will be performed. CBCT images will be obtained at baseline and 24 months after the treatment to evaluate the apical shadow. The primary outcome of this study is the success rate of RET 24 months postoperatively, which will be obtained by evaluating the clinical and radiographic outcomes. The secondary outcomes include the subjective response from the patient to thermal and electric stimuli, which reflects the responsiveness of regenerative pulpal sensory neurons. Safety will be evaluated via the analysis of the presence of adverse events during the study. The evaluators will complete standardised training prior to the study period. Two trained dentists will independently evaluate and disagreements will be resolved through a discussion with a third evaluator.

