#### Primary outcome measures

The therapeutic effect evaluation criteria are the following:
*Success*. After RET, the tooth is asymptomatic, with an absence of percussion pain, bone adhesion percussion sound, loosening, tenderness, mucosal swelling, sinus, or fistula. The radiographic examination demonstrates the absence of an apical shadow or a reduced apical shadow.*Failure*. After RET, the tooth is symptomatic, with symptoms of apical infection such as pain and fistula. The radiographic examination demonstrates a new-onset apical shadow or an enlarged apical shadow.

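### Carrying the last observation forward is a weak primary rule for 24-month success: it can record a pre-event or not-yet-healed state as the final result and counts filled values as observed

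*Protocol article*

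**What the plan says.** All references are to the Protocol article.

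- **Endpoint** (Outcome measures): "The primary outcome of this study is the success rate of RET 24 months postoperatively". Under Primary outcome measures, the radiographic part of success reads "The radiographic examination demonstrates the absence of an apical shadow or a reduced apical shadow". No imaging modality is named there.
- **Visits and imaging** (Outcome measures): "Variables will be measured at baseline and at 1, 3, 6, 12, 18, and 24 months after the treatment". At every visit, "At each appointment, a clinical examination, a periapical radiograph, and pulp tests (thermal and electric) will be performed". The second modality is more limited: "CBCT images will be obtained at baseline and 24 months after the treatment to evaluate the apical shadow".
- **Missing data** (Statistical analysis, main outcome): "the last observation carry forward method will be adopted to fill the validity analysis". The article explains that an incomplete case "will be transferred to the final result of the test with the last observation data". This is the only missing-data rule given for efficacy. The success rates are compared by a chi-square test, or by logistic regression if baseline variables are unbalanced.
- **Dropout** (Dropout criteria): the reasons are serious adverse events judged to require termination, with severe internal or external root resorption and tooth fracture as examples; poor compliance; and withdrawal of consent.
- **Size** (Sample size): 346 patients, 173 per group, alpha 0.05, power 80%. No success rates or dropout allowance are stated.

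**The concern.** The trial asks what state the tooth is in at 24 months. For a patient who leaves, the rule answers with the state at some earlier visit. Three features of this trial make that substitution hard to defend.

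1. The earlier visit differs in time, and its scheduled imaging is film without CBCT. A shadow that has not yet shrunk does not meet the success definition at that visit, whatever it would do by month 24. A tooth that is quiet at that visit can still fail later.
2. Leaving can be caused by the tooth itself. If a patient is withdrawn for fracture or severe resorption, the last scheduled visit may have been satisfactory, and that visit becomes the final result.
3. The filled values enter the test as if they had been observed at month 24, so the standard error takes no account of what is missing.

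At stake are the success rate in each arm, the comparison between arms, and the width of the confidence interval for the primary result.

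**Working it through.** **Inputs from the article.** 173 per arm; alpha 0.05 (sidedness not stated, taken as two-sided); chi-square test; post-treatment visits before the endpoint at 1, 3, 6, 12 and 18 months.

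**Assumed inputs.** Success, dropout and carried-forward rates are not in the article, so every rate below is an assumption. The figure of 173 cannot be reproduced without rates. Two-sided pairs that fit it closely with no dropout include 61% v 75%, 69% v 82% and 74% v 86%. I use 80% v 90.6%, which gives 80% power at 173 per arm.

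**Formulas.** With true rate p, proportion lost m and success rate c among carried values, the analysed rate is (1 − m)p + mc. For analysed rates a and b with difference d = b − a and mean p̄:

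- s0 = √[2p̄(1 − p̄)/n]
- s1 = √[a(1 − a)/n + b(1 − b)/n]
- rejection probability = Φ((d − 1.96·s0)/s1) + Φ((−d − 1.96·s0)/s1)

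**Step 1: a true difference, 20% loss in each arm.**

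- No loss: 80% v 90.6%, d = 10.6 points, power 80%.
- All carried values success: 0.8×0.80 + 0.2×1 = 84.0%; 0.8×0.906 + 0.2×1 = 92.5%; d = 8.5 points; s0 = 0.0346, s1 = 0.0343; power 69%.
- Half carried as success: 0.8×0.80 + 0.2×0.5 = 74.0%; 0.8×0.906 + 0.2×0.5 = 82.5%; d = 8.5 points; s0 = 0.0444, s1 = 0.0441; power 48%.
- Completers only, about 0.8×173 = 138 per arm at 80% v 90.6%: power 70%.

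So 69% is almost the same as the completers' figure, and that fall from 80% is mostly lost information. The fall to 48% is largely a cost of the rule itself. At 10% loss the two carried-forward figures are 75% and 63%.

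**Step 2: no true difference, 80% in both arms, loss unrelated to outcome.**

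| Loss | Carried success | Analysed rates | False rejection |
|---|---|---|---|
| equal | same in both arms | equal | about 5% |
| 10% v 15% | 50% | 77.0% v 75.5% | 6% |
| 10% v 20% | 50% | 77.0% v 74.0% | 10% |
| 10% v 30% | 50% | 77.0% v 71.0% | 25% |
| 10% v 30% | 70% | 79.0% v 77.0% | 7% |

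Completers would show 80% in both arms in every row, so the excess over 5% comes from the rule.

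**Step 3: no true difference, outcome-related loss.** Suppose 80% of all randomised teeth succeed in each arm, 5% v 10% drop out, and every dropout is a true failure carried as a success. The analysed rates are 80 + 5 = 85% v 80 + 10 = 90%, and false rejection is 29%. Completers alone would also be distorted here: 0.80/0.95 = 84.2% v 0.80/0.90 = 88.9%.

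**Step 4: precision.** If filled values carry no information about month 24, counting them as observed understates the standard error by 1 − √(1 − m): 2.5% at m = 5%, 5.1% at 10%, 7.8% at 15% and 10.6% at 20%. Where earlier visits do predict month 24, the shortfall is smaller.

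**Step 5: patients lost before month 1.** Success is defined after treatment. Such a patient has only a baseline record, so there is no valid value to carry.

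**The case against.** The strongest reply is that nothing in the article shows the rule will do much harm. No dropout rate is given. With equal loss and equal carried rates, false rejection stays near 5%. The 25% figure needs 10% v 30% loss with only half of carried values successful, and the 29% figure needs every dropout to be a failure recorded as success. A carried success rate of 50% may be low: teeth without periapical lesions are eligible, patients must be free of symptoms before the second-visit procedure, and any reduction in the shadow counts. This stands. The scenarios show a range and are not a forecast.

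A reader might infer several stronger things that the documents do not support:

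- **That a CBCT-read endpoint is replaced by a film-read one.** CBCT at 24 months is stated to be for the apical shadow, but the success definition names no modality and a film is also taken at 24 months.
- **That the carried result is always early.** It may come from month 12 or 18.
- **That bias is established, in a known direction.** It depends on who leaves, when and why.
- **That the rule itself costs 11 points of power (80% to 69%).** Completers only would have 70%.
- **That resorption or fracture already counts as Failure.** The Failure definition lists neither, so assigning such withdrawals to Failure would alter the outcome definition.

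An analysis plan that is not shown may contain sensitivity analyses, so their absence from the article is no fault. That does not answer the point, because the article itself fixes the primary rule.

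**Conclusion.** The concern holds in a limited form. The article commits the primary analysis to a single-value fill that is unbiased only if dropouts' last recorded status equals their status at 24 months. The visit schedule and the dropout criteria give concrete reasons to doubt that equality, most clearly where the tooth itself causes the withdrawal.

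The size is conditional on assumed rates. The effect can be negligible under balanced, uninformative loss. It can also be serious: power of 48% in place of 70% for completers, or false rejection of 25% to 29%, in the adverse cases. At 20% missing, the standard error is understated by up to about 11%. The article does not allow one of these to be picked as the likely result, which is itself a reason not to rest the primary result on this rule.

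**What to change.** - **Primary rule.** Replace last observation carried forward with multiple imputation by arm in all randomised patients, using baseline lesion status, centre and all earlier clinical and radiographic visits. Keep last observation carried forward only as a supplementary analysis.
- **Sensitivity.** Add missing-as-failure and a tipping-point analysis. These matter because step 3 describes loss that depends on the unseen outcome, which imputation from earlier visits may not fully correct.
- **Definitions.** Reconcile the Dropout criteria with the Primary outcome measures, so that withdrawal for a tooth-related event has a stated primary-outcome status and cannot be overwritten by an earlier success. Which status it takes is for the investigators to decide and record before analysis.

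The cost is revised wording and some extra programming. The article names SPSS 20.0 but does not say whether the planned installation supports multiple imputation, so that should be checked. No visit or procedure changes. The Trial status section says that recruitment was under way, so at that stage the change could still be made before analysis.
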